### Delivery and fidelity

Therapists in both groups will receive specific training on how to prepare the intervention, how to guide the parents and how to set the therapy goals.

For both groups, an intervention diary will be given to the caregiver, and must be completed on the days of the intervention at home. The “MY HOME STIMULATION DIARY”, contains items such as date, start and end time of the intervention, the duration of each proposed activity, which toys were used, and if there were any difficulty during the intervention. The diary will be delivered online and reviewed by the therapist weekly. To guarantee the fidelity of the interventions, a check-list will be drawn up with all the points that the parents must carry out during the intervention. Opportunities to discuss these points, and the difficulties of the intervention will be offered during the weekly tele-care sessions.

### Outcomes measures

After acceptance to participate in the study and before randomization, the basic measures and anthropometric data, general health data and socioeconomic aspects of each family / infant will be collected (T0).

All assessments will be conducted online. The study will have at least 4 evaluators. All evaluators are trained physiotherapists, with experience in the field of pediatrics and in the scales applied. Evaluators will be trained on the application, scoring and interpretation of all scales. For all outcomes, the inter-examiner and intra-examiner reliability calculation will be calculated using the Intraclass Correlation Coefficient (ICC). For the analysis of the ICC, the classification recommended by Weir (2005) will be considered: null: 0.00; weak: 0.01 to 0.30; regular: 0.31 to 0.60; strong: 0.61 to 0.90 and excellent: 0.91 to 0.99; and full = 1.00.

The primary outcomes will be motor capacity that will be assessed by the Infant Motor Profile (IMP) and Alberta Infant Motor Scale (AIMS). The secondary outcomes will be: a) participation assessed by the Young Children’s Participation and Environment Measure (YC-PEM), b) the parent-infant interaction assessed by the Parent-Child Early Relational Assessment (PCERA), c) the environmental changes assessed by the Affordances in the Home Environment for Motor Development (AHEMD). The assessment instruments according to the International Classification of Functioning, Disability and Health (ICF) biopsychosocial scheme are shown in Fig. 3.

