**Methods:**

Randomized controlled trial. Infants at risk, with 3 to 9 months corrected age, will be included, and randomized into two groups: control group (conventional guidelines) and experimental group (task, environment and participation in context-specific home program). Infants will be assessed for motor capacity (Infant Motor Profile and Alberta Infant Motor Scale); participation (Young Children’s Participation and Environment Measure) and environment factors (Parent-Child Early Relational Assessment; Affordances in the Home Environment for Motor Development). The intervention period will be 10 weeks, and evaluations will be carried out before and after that period. All the assessment and intervention procedures will be carried out online, with instructions to parents for home therapy. The statistical analysis will be guided according to the distribution of the data, and a significance level of 5% will be adopted. All ethical approvals were obtained by the Ethics Committee of the University of São Carlos (Case number 31256620.5.0000.5504). The protocol will follow the SPIRIT statement. Findings will be disseminated in peer-reviewed publications and presented at national and international conferences.

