## Objectives and hypotheses

The primary aim of the study is to compare the motor capacity of infants at risk for developmental delay receiving two types of telecare programs. The secondary objectives are to compare the following aspects between the two tele-care programs: a) compare frequency and involvement components of participation at home; b) compare parent-child interaction in aspects of parental behavior, child behavior and dyad of the relationship between; c) compare the availability of toys and affordances in the physical home environment.

We hypothesize that:Infants who receive the the STEP protocol will have higher scores on motor assessments than those who receive the control intervention;Infants who receive the STEP protocol will have higher scores on participation measures compared to the control intervention;Infants who receive the STEP protocol will have higher scores on parent-interaction and home environment measures compared to the control intervention;

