### Sample size

The study will have a non-probabilistic convenience sample. The sample calculation was performed a priori using the G*Power software. Sample size was determined based on the data obtained in the study by Hielkema [25], from the total score of the Infant Motor Profile (IMP) scale. An effect size of 0.23, statistical power of the test of 90% and statistical significance of 5% were considered. The sample calculation resulted in 52 participants. To guarantee a sufficient number of participants, the inclusion of 15% more participants was established in order to meet a possible dropout rate. Thus, the allocation of 30 participants in each group was determined.

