Young Children’s Participation and Environment	Secondary	Phone call	This is an instrument answered by the caregivers of young children. The YC-PEM presents internal consistency ranged from 0.68 to 0.96 for participation and 0.92 to 0.96 for environment [37]. Although it does not have validation for the Brazilian population, the scale will be used because it jointly assesses participation in activities and the environments that children attend, and is specific for younger children. The YC-PEM assesses the level of activity and participation and the quality of the environment through three sessions: home, daycare/preschool, and community. Higher scores are representative of greater participation and a facilitating environment.	Score of each session regarding frequency and involvement.	T0 and T2
Affordances in the Home Environment for Motor Development	Secondary	Online questionnaire	Evaluation of the quality and quantity of opportunities offered by the family and the environment for the infant’s motor development. The questionnaire is validated, self-explanatory, and is answered by the parents themselves [38]. The scale consists of an initial part, which contains items about the infant and the family (15 items), and three subscales: Indoor and outdoor physical space of the home (10 items), Daily activities (11 items) and Existing toys in the home (20 items) [39]. As it is a self-assessment and self-explanatory questionnaire, the format of this scale allows it to be sent through an electronic form, being self-administered by parents and caregivers, ensuring the reliability of the instrument’s application (Caçola et al., 2011). Scoring is performed by adding the scores for each subscale. Higher scores are representative of greater affordances and opportunities in the home environment. The scale has a maximum score of 49 points [39].	Total sum of the subitems of the scale	T0 and T2

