### Statistical analysis

The statistical analysis used will follow the standard principles for randomized controlled studies. The SPSS 17 software will be used for data analysis. The analysis of main interest of the study is the comparison between the groups at the end of the intervention. Data from participants who drop out of the study will be stored and all children entered initially (with assessment of the baseline measures) will be included in the intention-to-treat analysis, with a significance level of *p* < 0.05.

To test the difference between the two groups in maternal and infant characteristics (birth weight, gestational age, sex and corrected age) and in baseline measures (AIMS, IMP, YC--PEM, PCERA and AHEMD-IS) will be used the t test for parametric data and the Mann-Whitney test for non-parametric data. In order to verify the effect of the experimental intervention versus the conventional guidelines for primary and secondary outcomes, the t-test and the Mann-Whitney test will be used. The effect size will be calculated using Cohen’s d.

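### IMP and AIMS are both primary for one motor aim, with a single unsplit 5% level and a sample size built on IMP alone, so either the 5% error rate or the 90% power does not describe the primary claim

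*Protocol article*

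**What the plan says.** **Primary outcomes.** Under Objectives and hypotheses there is one primary aim: "The primary aim of the study is to compare the motor capacity of infants at risk for developmental delay receiving two types of telecare programs". Under Outcomes measures, two instruments carry it: "The primary outcomes will be motor capacity that will be assessed by the Infant Motor Profile (IMP) and Alberta Infant Motor Scale (AIMS"). Table 2 marks each as primary and gives each its own analysis variable: a percentile for AIMS and a weighted average for IMP. The matching hypothesis expects "higher scores on motor assessments than those who receive the control intervention" and does not say whether one scale or both must show this.

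**Level and power.** The abstract says "a significance level of 5% will be adopted". The Statistical analysis section includes all children "with a significance level of" p < 0.05 and compares the groups on primary and secondary outcomes by t-test or Mann-Whitney test. No split or order is given. The Sample size section takes its effect size "from the total score of the Infant Motor Profile (IMP) scale", with 90% power and 5% significance. AIMS does not enter.

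**Participation.** Secondary objective (a) is to "compare frequency and involvement components of participation at home". For YC-PEM, Table 2 gives the analysis variable as "Score of each session regarding frequency and involvement", and the sessions it describes are home, daycare/preschool and community.

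**The concern.** Two labelled primaries, one unsplit level and a power calculation on one of the two do not fit together. If a significant result on either scale counts as success, 5% is the error rate of each test but not of the motor claim. If both scales are needed, the claim is protected but its power is not the 90% stated. If only one scale reaches significance, the article offers no agreed reading, and the choice would be made after the results are known.

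The YC-PEM point is separate and smaller. The objective names two scores and the analysis table names six, so a reader cannot tell which participation results answer the objective.

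**Working it through.** **Inputs from the article.** Two primary scales, one score each; level 5%; effect size 0.23 from IMP; power 90%; 52 participants, then 15% more, giving 30 per group; 1:1 allocation; the comparison of main interest is at the end of the intervention, so the 5-week assessment is not a further primary test.

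**Assumptions.** Two-sided tests, since sidedness is not stated. The IMP-AIMS correlation r is not given, so a range is shown.

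**1. The plan's own figure.** 52 is reproduced by a repeated-measures ANOVA, group-by-time interaction, with f = 0.23, 2 groups, 2 measurements and an assumed correlation of 0.5 between measurements:
- noncentrality = f² × N × m / (1 − 0.5) = 0.0529 × 52 × 2 / 0.5 = 11.0, with 1 and 50 degrees of freedom, giving power 90.2%;
- with N = 50 the power is 89.0%, so 52 is the smallest even total;
- 52 × 1.15 = 59.8, rounded to 60, or 30 per group.

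The stated 90% is therefore the power of one test, on IMP.

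**2. If either scale is enough.** With both null hypotheses true:
- false finding in either direction = 1 − P(|Z1| ≤ 1.96 and |Z2| ≤ 1.96);
- false finding in favour of STEP = 1 − P(Z1 ≤ 1.96 and Z2 ≤ 1.96).

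At r = 0 these are 1 − 0.95² = 9.75% and 1 − 0.975² = 4.94%. For other values the bivariate normal distribution gives:

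| r | Either direction | In favour of STEP | Simulated t-tests, 30 per group, either direction |
|---|---|---|---|
| 0 | 9.75% | 4.94% | 9.7% |
| 0.5 | 9.07% | 4.54% | 9.2% |
| 0.7 | 8.35% | 4.17% | 8.2% |
| 0.9 | 7.04% | 3.52% | 7.0% |

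A single test gives 5% and 2.5%. Above r = 0.9 the excess shrinks: 6.5% at 0.95 and 5.7% at 0.99, either direction.

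**3. If both scales must succeed.** Whenever at least one null hypothesis is true, the chance that both tests are significant cannot exceed 5%, so no split is needed. Power is at most that of the weaker test. The article gives no power for AIMS. If it were also 90% (an assumption), joint power would lie between 1 − 0.10 − 0.10 = 80% and 90%, depending on r.

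**4. If the level were split, 2.5% each.** The family error is at most 4.94%. On the planning model of step 1, power is 83.9% with 52 evaluable infants and 89.3% with 60; 90% needs 62. These figures describe that planning model, not the end-of-intervention t-test in the analysis section.

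**5. YC-PEM count.** The objective has 1 setting × 2 components = 2 scores. Table 2 has 3 settings × 2 components = 6. Four scores lie outside the stated objective.

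**The case against.** **This is content for an analysis plan.** Multiplicity rules often sit in a document not shown here, and the absence of such a rule from a journal article would not be a finding. That stands. But the article itself fixes the number of primary outcomes, the single level and the basis of the sample size, and these are the three elements that do not agree.

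**The text does not say either scale is enough.** Also correct. The hypothesis uses the plural for motor assessments and can be read as requiring both scales. A reader might infer that the trial's false-positive rate simply is 7-10%. The article does not support that: the figure holds only under the either-scale reading, and its upper end needs uncorrelated scales, which is implausible for two motor scales applied to the same infants by assisted filming. The figure also counts false differences against STEP, although the hypothesis is directional.

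**YC-PEM.** A reader might infer that the extra participation scores add to the error of the motor claim, or that all listed outcomes form one family. They do not: YC-PEM is secondary, and the article never joins primary and secondary outcomes in one claim. Nor does the article give attendance figures to show that the daycare or community scores would not apply. The non-home scores also have some rationale. The second hypothesis concerns participation without limiting it to the home, and the training of STEP therapists covers participation in the community. What remains is a mismatch between objective (a) and Table 2.

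**Other repairs would work.** Requiring both scales, a Holm procedure or a split level would each settle the matter. Table 2 describes AIMS as validated in Brazil, which is a fair reason to hesitate before ranking it second. The case for IMP first is that the sample size already rests on it.

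**Conclusion.** The concern holds in conditional form. Under the either-scale reading, the two-sided chance of a false motor finding is about 7-10% for r from 0 to 0.9, and 3.5-4.9% for a false finding in favour of STEP, against 5% and 2.5% for one test. Under the both-scales reading, the error is at most 5%, but the stated 90% power does not describe the primary claim. Either way, one stated figure does not belong to the claim it appears to support. The arithmetic is secure; the size depends on a correlation and a success rule that the article does not give. The matter should be settled before analysis, but it does not invalidate the design. The YC-PEM mismatch is a separate, minor inconsistency of scope.

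**What to change.** Before any outcome data are seen by group:

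1. Name the IMP score at T2 as the single primary outcome. Define it as the weighted average in Table 2, and reconcile this with the total score cited under Sample size and with the summing of subscales in the Table 2 description.
2. Make AIMS at T2 the first secondary outcome, tested at 5% only if IMP is significant. This fixed sequence holds the error for the two motor tests at 5% and leaves the stated basis of the sample size unchanged.
3. Name home frequency and home involvement as the YC-PEM secondary outcomes, and label the four daycare and community scores exploratory.

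**Cost.** A protocol amendment and a change to the registry entry. The trial was registered in September 2020 and the article cites amendment 02, so the amendment should record that no outcome data had been seen by group. The real loss is that AIMS alone could no longer make the trial positive. If the sponsor cannot accept that, a level split at 2.5% each is possible, but it needs 62 evaluable infants for 90% power on the planning model. Requiring both scales is also possible, at a cost in power.

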**Fig. 3 Fig3:**
[figure not shown]
Assessment instruments organized in the CIF scheme. Legend: GMA: General Movements Assessment; PCERA - Parent-Child Early Relational Assessment; IMP - Infant Motor Profile; YC-PEM - Young Children’s Participation and Environment Measure; AIMS - Alberta Infant Motor Scale; AHEMD - Affordances in the Home Environment for Motor Development

All these measures will be applied before the intervention (T0). After 5 weeks of intervention (T1) both groups will be evaluated by the AIMS and IMP, to verify the evolution and possibly redirect the activities. After completion of the intervention (T2) all outcomes will be applied again. More details about the outcomes and their applications are found in Table 2.

**Table 2 Tab2:** Study outcomes

Scale	Outcome	Assessment method	Description	Statistical analysis	Timepoint
Alberta Infant Motor Scale	Primary	Filming with assistance	The scale assesses the motor skills of infants from 0 to 18 months [31]. It is validated for the Brazilian population [32]. Studies demonstrate that home video evaluation of this scale, performed by parents, has validity [33, 34]. We performed the inter-rater reliability analysis with high-risk infants and found values above 0.9, indicating high reliability. The scale consists of 58 items, in which the child is evaluated in the four postures: prone, supine, sitting and standing. In the application of the scale, when the infant is able to perform a certain item, a score of 1 is generated and when he is unable to perform it, a score of 0 is obtained, totaling up to 58 points. The sum of all scales defines the gross AIMS score. This score is transformed into a percentile that represents the child’s motor development [31, 32].	AIMS percentiles	T0, T1 and T2
Infant Motor Profile	Primary	Filming with assistance	Qualitative assessment of spontaneous motor behavior in childhood, with high interobserver reliability (correlation coefficient of 0.95) and strong relationship between their scores and the findings of neurological exams [35]. We performed the inter-rater reliability analysis with high-risk infants and found values above 0.8, indicating high reliability. The IMP was applied because it evaluates beyond the motor milestones, the size of the repertoire, variability and adaptability of the child when performing the movements. The IMP assess infants from 3 to 18 months, or until they have a few months of experience walking independently. The evaluation is recorded for later scoring, and the motor behavior is evaluated in the following postures: supine, prone, sitting, standing and walking. The IMP has 80 items subdivided into five scales: variability-repertoire; variability- ability to select; symmetry; fluency and performance. The scores of each subscale are summed. Higher scores represent greater motor performance.	Weighted average score	T0, T1 and T2
Parent-Child Early Relational Assessment	Secondary	Spontaneous filming	This instrument assesses the early relationship between parents and children aged 0 to 4 years. Through a 5-min film, the scale determines the quality of behavior and the amount of affection in the relationships between parents and children, during the interaction in activities such as food, predetermined tasks, play / free games and separation / meeting between parents and children [36]. It has high reliability in the father (0.86–0.91) and child (0.83–0.87) subscales [36]. The instrument has 65 items subdivided into: parental behavior; child characteristics and dyad of the relationship between them. Higher scores represent a quality of positive interaction.	Total of each subscale: mother / child / dyad	T0 and T2
Young Children’s Participation and Environment	Secondary	Phone call	This is an instrument answered by the caregivers of young children. The YC-PEM presents internal consistency ranged from 0.68 to 0.96 for participation and 0.92 to 0.96 for environment [37]. Although it does not have validation for the Brazilian population, the scale will be used because it jointly assesses participation in activities and the environments that children attend, and is specific for younger children. The YC-PEM assesses the level of activity and participation and the quality of the environment through three sessions: home, daycare/preschool, and community. Higher scores are representative of greater participation and a facilitating environment.	Score of each session regarding frequency and involvement.	T0 and T2
Affordances in the Home Environment for Motor Development	Secondary	Online questionnaire	Evaluation of the quality and quantity of opportunities offered by the family and the environment for the infant’s motor development. The questionnaire is validated, self-explanatory, and is answered by the parents themselves [38]. The scale consists of an initial part, which contains items about the infant and the family (15 items), and three subscales: Indoor and outdoor physical space of the home (10 items), Daily activities (11 items) and Existing toys in the home (20 items) [39]. As it is a self-assessment and self-explanatory questionnaire, the format of this scale allows it to be sent through an electronic form, being self-administered by parents and caregivers, ensuring the reliability of the instrument’s application (Caçola et al., 2011). Scoring is performed by adding the scores for each subscale. Higher scores are representative of greater affordances and opportunities in the home environment. The scale has a maximum score of 49 points [39].	Total sum of the subitems of the scale	T0 and T2

Assessments will take place in four ways, depending on the instrument in question:SPONTANEOUS FILMING: video recording of the infant by parents, on scales that do not require simultaneous instruction. Parents will receive an online document, with all instructions related to the positioning of the infant, in which case the filming should take place, use of toys or stimuli. The PCERA instrument will be applied in this way.FILMING WITH ASSISTANCE: parents will be asked to take part in a video-based telehealth appointment with the evaluator. In the video interaction, the researcher will guide the parents in relation to how to carry out the activities, which positions and stimuli are recommended according to the components of the scale. Parents will apply activities on the infant simultaneously to the video transmission, so that the researcher can correct and guide caregivers in real time. The video stream will be recorded for later scoring. The following instruments will be evaluated in this way: AIMS and IMP.ONLINE QUESTIONNAIRE: the assessment scales that can be self-completed by caregivers will be transformed into online questionnaires. The AHEMD instrument will be evaluated in this way.PHONE CALL: assessments that must be answered by the caregivers but applied by the therapist. The YC-PEM instrument will be evaluated in this way.

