## Background

Functioning refers to the dynamic and positive interaction between the components of body structure and function, activity and participation, under the influence of environmental and personal factors [1]. Currently, an example of the impact of environment factors on the quality of life is the social barrier caused by COVID-19 pandemic. The high number of people infected by COVID-19 has led to an overload of the health care system, even in high-income countries [2–5].

Social isolation has been the main strategy to delay the spread of the virus [6, 7]. Although social distancing has an essential role in the prevention of the COVID-19 spread, studies have shown that social distancing impacts health conditions [8], especially for persons that are physically vulnerable [9]. This occurs because social distancing affects the maintenance of other essential health services [10, 11].

Children at risk for developmental delay might be impacted by social isolation since they usually require the use of health services. Infants at risk for developmental delay are those who have some intrinsic biological risk or risks associated with the mother [12, 13], as prematurity, low birth weight, hypoxemia, use of ventilatory support, cardiorespiratory resuscitation, and prolonged hospitalization [12–14]. These infants usually present delayed motor, cognitive, and behavioral development, besides limitations on functional activities and restricted participation [15].

Due to social isolation, some therapeutic services provided to these children may be limited. Tele-care seems to be an economical way to expand access to infants at risk to health care during social isolation [16]. Tele-care has the advantage of enabling the performance of functional activities by the infants in the home environment, as well as involvement of the family in the rehabilitation process [16]. In addition, tele-care could be inexpensive for patients and institutions, help prevent the spread of the virus, and provide care for these infants.

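### AIMS, one of two primary outcomes, is analysed as an unadjusted percentile at T2; an age-normed z-score adjusted for T0 would be a cheap improvement, chiefly if the infants lie well below the norm.

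*Protocol article*

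**What the plan says.** The section Outcomes measures states: "The primary outcomes will be motor capacity that will be assessed by the Infant Motor Profile (IMP) and Alberta Infant Motor Scale (AIMS"). It gives no rule that both must succeed.

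Table 2 describes a raw total of up to 58 points ("The sum of all scales defines the gross AIMS score") and continues: "This score is transformed into a percentile that represents the child". The table's column for the statistical analysis names "AIMS percentiles". The percentile is therefore a stated choice and not a detail left open.

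The section Statistical analysis adds: "The analysis of main interest of the study is the comparison between the groups at the end of the intervention". For primary and secondary outcomes, "the t-test and the Mann-Whitney test will be used". On the effect measure: "The effect size will be calculated using Cohen"'s d. No adjustment for the T0 value is described there.

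On where the sample might lie on the AIMS norm, the article has only a qualitative remark in Background: "These infants usually present delayed motor, cognitive, and behavioral development". It gives no AIMS mean, SD or percentile distribution.

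**The concern.** A percentile is a non-linear function of a child's position relative to age norms. Far below the norm, a real motor gain moves the percentile by a few points. Near the median, the same gain moves it by many. A mean difference in percentiles, and a Cohen's d built on it, therefore mixes the size of the motor gain with the location of the sample. Within a sample, it gives more weight to infants who start higher.

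The trial enrols infants at moderate to high risk, so a low location is plausible. At stake are the interpretation of a primary effect estimate and, if the t-test is used, some power.

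**Working it through.** **The plan's own figure.** No power or sample size is stated for AIMS. The stated 52 participants (26 per arm; 60 after 52 × 1.15 = 59.8) rest on the Infant Motor Profile total score. The 52 reproduces as a repeated-measures group-by-time interaction with f = 0.23, two time points and an assumed correlation of 0.5: λ = 0.23² × 52 × 2 / (1 − 0.5) = 11.0, power 0.902. This calculation makes no claim about AIMS. It is used here only for the 26 per arm.

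**Assumptions, none of them from the article.** AIMS is expressed as an age-normed z-score, normal within arms with SD 1; percentile = 100 × Φ(z). The mean z is varied because the article does not give it.

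**Step 1: compression for one infant.** A gain of 0.5 SD is worth 100 × [Φ(z + 0.5) − Φ(z)] percentile points:

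| Starting z | Percentile points gained |
|---|---|
| -2.5 | 1.7 |
| -2 | 4.4 |
| -1.5 | 9.2 |
| -1 | 15.0 |
| -0.5 | 19.1 |

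**Step 2: the group mean.** With SD 1, the mean percentile is 100 × Φ(μ/√2). If every infant gains 0.5 SD, the mean difference is 100 × [Φ((μ + 0.5)/√2) − Φ(μ/√2)]. The same true gain reads differently by location, and its sources shift:

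| Mean z | Mean difference (points) | Share from highest third | Share from lowest third |
|---|---|---|---|
| -1 | 12.2 | 47% | 13% |
| -1.5 | 9.5 | 60% | 7% |
| -2 | 6.6 | 73% | 3% |

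Cohen's d moves too. A fixed 0.92 SD effect gives d on percentiles of 0.92, 0.79 and 0.70 at control means of -1, -2 and -2.5.

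**Step 3: power of the planned t-test, 26 per arm.** Two effect sizes were simulated (20,000 trials for 0.92 SD, 4,000 for 0.5 SD). Entries are z-score versus percentile:

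| Mean z | Effect 0.92 SD | Effect 0.5 SD |
|---|---|---|
| 0 | 90% v 89% | not run |
| -1 | 90% v 88% | 43% v 39% |
| -1.5 | 90% v 85% | 43% v 37% |
| -2 | 90% v 80% | 43% v 31% |

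The loss is about 1 to 4 points at -1 or higher, 5 to 6 at -1.5 and 10 to 12 at -2. Mann-Whitney has identical power on z and percentile in every scenario, because the ranks are the same.

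**Step 4: adjusting for T0.** With an assumed T0–T2 correlation of 0.6 and a 0.5 SD effect, ANCOVA power (z versus percentile) is 60% v 54% at mean z -1, 60% v 48% at -1.5 and 59% v 40% at -2. Changing the scale first and then adjusting, the route at -1.5 is 37% → 43% → 60%: 6 points from the scale and 17 from T0. At -2 it is 31% → 43% → 59%: 12 and 16. The split depends on the order. Adjusting the percentile first at -2 gives 31% → 40% → 59%, with 9 points from T0 and 19 from the scale.

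**Step 5: the raw score.** Without age adjustment the raw score is worse than the percentile. With assumed slopes of 4 to 5 points per month, within-age SD of 4 to 7 points and a 6-month age spread, t-test power for a 0.92 SD effect is 0.36 to 0.64, against 0.80 to 0.88 for percentiles. With T0 and age in the model, under an assumed curved age norm and a 0.5 SD effect, raw-score power is about 50 to 55%, against 31 to 42% for the planned percentile t-test. Compared with a percentile that is itself adjusted for T0, the raw-score model is clearly better only at mean z -1.5 or lower, and slightly worse near the norm.

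**The case against.** The percentile has a purpose: it places infants who enter at 3 to 9 months corrected age on one scale, and Step 5 shows that dropping it without handling age would do harm. Entry is by biological risk factors and not by a motor score, and infants with already diagnosed primary diseases are excluded, so a mean z of -1.5 or -2 is not established. The Abstract says the analysis will follow the distribution of the data. Strong low-tail compression gives skewed percentiles, which is when Mann-Whitney would be chosen, and that test loses nothing. The raw total is a sum of pass/fail items and need not be an interval scale either.

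Most of this stands. It removes any claim that the plan is wrong or that a large power loss is certain. It does not remove the interpretive point: Cohen's d is planned whichever test is used, and neither two-sample test uses the T0 measurement.

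A reader might also infer that the 10- to 20-point gaps in Step 4 are losses under the plan. They are not, because that section plans no T0-adjusted model. Nor may one infer that a few infants near the median will drive the result. The shares in Step 2 hold only for the assumed locations.

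**Conclusion.** This is a cheap improvement and not an error. AIMS is fixed as a percentile, compared without T0 adjustment and summarised by Cohen's d. If the sample lies well below the norm, the estimate is location-dependent and weighted to the less delayed infants. The scale alone then costs the t-test the modest amounts in Step 3; near the norm the cost is negligible. Everything quantitative rests on normal z-scores, SD 1, 26 per arm and assumed means and correlation.

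The tempting stronger reading, that the percentile makes this primary outcome insensitive in the infants the trial is about, needs an AIMS distribution that the article does not give. Nor do the documents make the two primary outcomes jointly necessary, so a weaker AIMS analysis does not by itself decide the trial.

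**What to change.** In Table 2 and the section Statistical analysis, define the AIMS analysis as the T2 age-normed z-score, compared between groups in a linear model with the T0 z-score as covariate. If the available norms do not support z-scores, use the raw 0 to 58 score with T0 raw score and corrected age as covariates, and never the raw score without age. Report percentiles descriptively.

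The data are already to be collected, so no new assessments are needed. The costs are that a regression model replaces the two-sample test, the effect is no longer in percentiles, and the raw-score version depends on an adequate age adjustment across the 3- to 9-month entry range. The section Intervention already promises therapy dose as a covariate, which a two-sample test cannot accommodate, so a model is needed in any case. If the percentile is kept, adding T0 still recovers part of the power.
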